### 2.1.7 Recruitment

#### Recruitment of physicians

Our feasibility survey study (April–August 2016) demonstrated there were 352 physicians (general practitioners, ear-nose-throat specialists, and paediatricians) who were willing to participate in our main study and they had 705 paediatric patients with AOM in the past seven days. For our pilot study, we identified 50 physicians from the most feasible seven hospitals located in DKI Jakarta who were willing to participate in our study and had approximately 97 paediatric patients with AOM in a week.

#### Recruitment of participants

After physicians deliver the patient information and obtain the consent from the eligible children, they will use the eligibility and randomisation form to assist them in stratifying the children based on their AOM severity. Physicians then will complete other CRFs, as the following: baseline history form and outcome form. Physician will assist the parents to complete the symptom diary. The similarity on the forms and sequences of both outcome CRF and symptom diary will help parents to be able to fill those correctly.

## 2.3 Assignment of interventions

### 2.3.1 Allocation

#### Sequence generation and implementation

All children and their parents who are eligible and consented will be enrolled, and stratified based on their AOM severities or clinical features. The randomisation process will be performed by the

appointed nurse who will randomly allocate children to either prednisolone and expectant observation or control (expectant observation alone) in the mild group and either antibiotic with prednisolone or control (antibiotic alone) in the severe group. A permuted block randomisation sequence will be computer-generated by the Centre for Research in Evidence-Based Practice Bond University, Gold Coast, Australia. Random numbers will not be disclosed to the outcome assessors (i.e. participating clinicians and audiologists/tympanometry technicians), to ensure allocation concealment. Batches of intervention packages will be dispatched to participating centres from a central pharmacy facility at the Clinical Research Supporting Unit, Faculty of Medicine Universitas Indonesia (CRSU FMUI).

### ***Allocation concealment mechanism and implementation***

The information of the eligibility and stratification which is provided by the participating physicians will help the appointed nurses to obtain the information from the randomisation website, whether the children will be allocated to the prednisolone or control group, identified by the 2-digit patient ID numbers. During the consultation, the physician will prescribe study medication for every subject with the dose based on the patient age and insert the prescription in the CRF folder. The nurse who performs the randomisation will give the prescription to the subjects who are allocated to the intervention group (prednisolone group). The subject then will give the prescription to the pharmacy, where the pharmacist will prepare the prednisolone by crushing the tablets, mixing them with sweeteners, packing the prednisolone mixed powder in a daily individual paper-pack for five days, and dispense these to the subjects along with instructions for preparation. The pharmacist will record the dispensing on the form provided by the study for this purpose.

### **2.3.2 Blinding (masking)**

In this study, the appointed nurses and the children and their parents will know the allocation of the intervention. We will ensure that the participating physicians and the audiologists/tympanometry technicians will be blinded to the intervention allocation during the study.

### ***Emergency unblinding***

The unblinding process should be done if there are serious adverse events and limited only to that particular participating physician.

## **2.4 Data collection, management, and analysis**

### **2.4.1 Data collection methods**

We will assess the outcomes using CRFs, patient symptom diary, and feedback forms. The CRFs consist of eligibility-and-randomisation, baseline history, outcomes, serious adverse events (if applicable), and drug dispensing and returned forms. The outcome form will record the severity of pain and overall symptoms with their durations using VAS and AOM-SOS, as well as the resolution of AOM signs using otoscopic and tympanometry examinations (for the mechanistic study).

We will identify the recruitment rate by assessing the proportion of children who provide their consents divided by the proportion of consultations with potentially eligible children during the trial. We will use the informed consent and a study recruitment log book to record the reason(s) why children were not randomised.

We will assess the success of the study procedures using feedback forms. On the feedback form, patients and their parents and participating physicians will rate their understanding and challenges

they have during the implementation of study procedures (e.g. obtaining the randomised 2-digit patient ID numbers and their allocation of the treatment, completing the informed consent forms and CRFs) using grading scale ranged from one to five (1=very easy; 2= easy; 3=moderate/neutral; 4=difficult; 5=very difficult).

To assess the ability to measure planned outcomes in main study, we will also use a feedback form to identify the understanding, the challenges, the complexity of the outcome assessment tools utilised for this study (e.g. CRFs and patient symptom diary which includes VAS and AOM-SOS) from the perspective of the patients and their parents and the participating physicians. The CRFs and symptom diary will record the clinical history and symptoms (e.g. VAS, AOM-SOS), as well as physical examination (e.g. temperature, blood pressure, otoscopic examination if feasible). This information will be obtained from the perspectives of the patients and their parents and the clinicians.

The VAS is acknowledged as a well-established and validated scale for assessing pain [41]. It has a 100-mm horizontal scale with ‘no pain’ anchor at the left endpoint and ‘the most severe pain’ at the right endpoint of the scale. The patient will mark a vertical line along the horizontal line as the representation of their pain level. The scale will be determined by measuring the distance from the left endpoint (‘no pain’) to the marked line [42]. A 10-mm difference has been reported to indicate a clinically significant change [43,44]. The AOM-SOS is used to assess the severity of other AOM-relevant symptoms daily, particularly in non-verbal children. Table 2 illustrates several AOM-related symptoms described as “no”, “a little”, and “a lot”. This scale was developed as an outcome reporting tool scoping symptom and activity limitation due to AOM in the proceeding 12 to 24 hours [45]. Shaikh et al. [45] used the mean of 4.2 points as a minimal important difference. We have translated the original English version of AOM-SOS to Indonesian version of AOM through forward and backward translation process.

**Table 2.** Acute otitis media severity of symptoms scale (AOM-SOS) [45]

| We are interest finding out how your child has been doing. For each question, please place a check mark in the box corresponding to your child’s symptoms. Please answer all questions |                          |                          |                          |
|-----------------------------------------------------------------------------------------------------------------------------------------------------------------------------------------------|--------------------------|--------------------------|--------------------------|
|                                                                                                                                                                                               | No                       | A Little                 | A Lot                    |
| Over the past 12 h, has your child been tugging, rubbing, or holding the ear(s) more than usual?                                                                                              |  |  |  |
| Over the past 12 h, has your child been crying more than usual?                                                                                                                               |  |  |  |
| Over the past 12 h, has your child been more irritable or fussy than usual?                                                                                                                   |  |  |  |
| Over the past 12 h, has your child been having more difficulty sleeping than usual?                                                                                                           |  |  |  |
| Over the past 12 h, has your child been less playful or active than usual?                                                                                                                    |  |  |  |
| Over the past 12 h, has your child been eating less than usual?                                                                                                                               |  |  |  |

Over the past 12 h, has your child been having fever or feeling warm to touch? ☐ ☐ ☐

---

The compliance to the study and study drug will be identified by assessing the completion of CRFs and symptom diary, particularly on the attendance of patients and the parents on their scheduled follow-up visits, the completion of the trial drug based on the symptom diary and the left-over drug. We will identify the parents who have low literacy during the informed consent process. For parents who have low literacy, we will visit their home one day after the initial visit to identify a person who lives nearby (e.g. family members, neighbours) that are able to assist the parents in completing the symptom diary, daily for two weeks. If there is no one can assist them, then the research personnel will assist them in completing the symptom diary by phone. If it is not feasible, we will visit their home daily to be able to assist them.

To assess the verification of sample size calculation for main study, we will use the CRFs.

To ensure that all the outcome data can be sufficiently collected and recorded properly according to prespecified plans, we will conduct an individual/institutional training for participating physicians prior the implementation of this pilot study. The training will include following sections: (1) introduction and summary of the study; (2) introduction of international clinical practice guidelines of AOM; (3) The diagnosis of AOM using otoscope and reporting the otoscopic results; (4) the introduction and dissemination of the principles of quality methodology clinical trial (e.g. eligibility, randomisation, blinding, outcome assessment) and good clinical practice (e.g. patient consents, confidentiality, data management); (5) practical steps of eligibility assessment, stratification, and randomisation; and (6) practical steps in completing study documentation (i.e. patient informed consents, CRFs, feedback forms, patient symptom diary).

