## Participant enrolment

In the main study, we will stratify eligible children by the clinical specialty (primary care or secondary/tertiary care) and severity of AOM (mild or severe). However, we only include ear-nose-throat-specialists (ENTs) who work at tertiary care in this pilot study. Therefore, we will stratify the children based on their AOM severity and then will randomly allocate these eligible children to receive either a single dose prednisolone for five days or without, as an addition to expectant

observation in the mild AOM group or as an addition to antibiotics according to physicians' preferences (e.g. antibiotic type, dose, duration) in the severe AOM group (see Figure 1).

[figure not shown]

**Figure 1.** Flow chart of the stratification and randomization of the study

Participating physicians will assess the eligibility of children who come to the hospital based on their symptoms and clinical features of AOM. The eligible children will then be stratified based on the severity of AOM to either mild or severe AOM group. This process will be assisted using an eligibility and randomisation form. The participating clinicians will then obtain a clinical history and perform a baseline examination, including general, otoscopic, and tympanometry examination. The results of these procedures will be recorded at the baseline history form and outcomes form. The tympanometry examination will be conducted by an audiologist or a tympanometry technician. The physician will assess and analyse the tympanometry findings and record the results in the outcome form. After these procedures, the children will be sent to the appointed nurse who will perform the randomisation and dispense the prescription for a study medication (prednisolone) if the patient is assigned to the intervention group.

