#### **2.4.3 Statistical methods**

For the recruitment rate, we report the outcome as the proportion of children in percentages (%). For the success of the study procedures and the ability to measure planned outcomes in main study, we will report the outcomes as the proportion of clinicians in percentages based on the grading

scale of their feedback reporting on prespecified outcome measure tools. For the compliance to study and study drug, we will report the outcomes as the proportion of children in percentages who attend the follow-up visits and complete the cycle of study drug.

To assess the verification of sample size calculation for main study, we will report this outcome as the proportion of children in each stratum (mild and severe AOM group) and those with pain at Day-3 after randomisation in the control group.

For the mechanistic sub-study, we will report continuous variables (i.e. the change in MEE at various time points (mean in days standard deviation), the duration of MEE) as a mean difference (MD) with 95% confidence intervals (CI) also the difference between two groups. We also will report the correlation between ear pain and other symptoms with the changes in MEE at various time points.

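### The feedback measure of the randomisation step asks people who do not carry it out and leaves out the nurses who do

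*Protocol*

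**What the plan says.** On measurement, section 2.4.1 states: "We will assess the success of the study procedures using feedback forms". It names the raters in the next sentence: "patients and their parents and participating physicians will rate their understanding and challenges". The scale runs from 1 (very easy) to 5 (very difficult). The first example given of a procedure to be rated is "obtaining the randomised 2-digit patient ID numbers and their allocation of the treatment"; completing consent forms and CRFs follows. Nurses are not among the raters there, and no other section gives them the form.

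On reporting, section 2.4.3 says of this outcome: "we will report the outcomes as the proportion of clinicians in percentages based on the grading" scale of their feedback. The ratings of patients and parents are not mentioned again.

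On who does the work, the text under Participant enrolment says that "the children will be sent to the appointed nurse who will perform the randomisation". Section 2.3.1 repeats this under sequence generation, with the "appointed nurse who will randomly allocate children to either prednisolone and expectant observation" or control. Its paragraph on concealment says that the physician's eligibility and severity information "will help the appointed nurses to obtain the information from the randomisation website". On masking, section 2.3.2 says: "We will ensure that the participating physicians and the audiologists/tympanometry technicians will be blinded to the intervention allocation during the study".

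**The concern.** Testing the stratification and randomisation processes is item (2) of the first objective in section 1.2. Obtaining the allocation result is part of component (3) of procedure success in section 2.2.4.1. The protocol chose an ease rating as its feedback measure for such procedures. A rating of ease is informative only when it comes from someone who has done the task.

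As written, the percentage reported for the allocation step would come from physicians. They do not use the website and are not meant to know what it returned. The nurses look up the allocation and then hand over or withhold the prescription, but they have no place on the form. A favourable percentage would therefore say little about how workable the step is for the people who operate it. Section 1.1.3 justifies the pilot partly by the lack of trial experience among most main-study physicians and facilities, so operators' experience is something the pilot ought to collect.

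**Working it through.** No formula or figure is involved. The check sets the operator of each step beside the rater and the reported group.

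| Step | Carried out by | Operator named as a rater in 2.4.1? | Operator's rating reported in 2.4.3? |
|---|---|---|---|
| Consent, eligibility, CRFs | Participating physician (Participant enrolment; 2.1.7; 2.6.3) | Yes | Yes |
| Assigning the severity stratum | Participating physician (2.1.7) | Yes | Yes |
| Obtaining ID and allocation from the website | Appointed nurse (Participant enrolment; 2.3.1) | No | No |
| Releasing the prescription to the prednisolone arm | Appointed nurse (2.3.1) | No | No |

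1. **Could clinicians in section 2.4.3 include the nurses?** No. Section 2.1 contrasts the nurse, who knows the allocation, with the clinicians, who do not. The two words denote different people in this protocol.

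2. **Do physicians come to perform the step in some other way?** No. Section 2.5.2 lets the nurse tell the physician the allocation when adverse effects are reported, after the day-3 pain outcome has been recorded. That may inform a physician about a particular child, but it does not make the physician a user of the website.

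3. **Could parents stand in for the nurses?** Only in part. They know the allocation and, in the prednisolone arm, take the prescription to the pharmacy, so they can comment as recipients. Section 2.4.3 does not carry their ratings into the reported result.

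4. **What else records the randomisation step?**
   - The registration data set lists the CRFs, including the eligibility and randomisation form, as the metric for this outcome.
   - Section 2.4.1 has a recruitment log book giving reasons why children were not randomised, and lists dispensing and return forms among the CRFs.
   - Section 2.3.1 has the pharmacist record dispensing.
   - Section 2.5.1 has an independent person assess recruitment and data entry.
   - Section 2.5.3 describes monitoring of the website system and interviews with investigators and coordinators.

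   These sources show whether the step was completed, and some problems may surface through them. None is described as collecting the nurses' own assessment of difficulty.

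5. **How much of the outcome is affected?** Section 2.2.4.1 lists three components of procedure success: consent, recruitment by the eligibility criteria, and stratification with randomisation. The first two, and the stratification half of the third, are done by physicians and can properly be rated by them. The gap is confined to the allocation half of the third.

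**The case against.** The best defence is that the pilot does measure randomisation, by the forms, log book and monitoring listed above, and that only a perception score is missing. This stands as far as completion of the step is concerned. A reader might infer that the pilot cannot assess the procedure at all, or that a website or dispensing fault known to nurses would stay hidden. The documents do not support either reading.

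A second defence concerns blinding. A reader might infer that asking physicians to rate how they obtained the allocation contradicts their masking or would unblind them. That is not shown. The item comes from a list of examples pooled over all raters, the form itself is not reproduced, and rating the difficulty of a process does not reveal its result. The physicians' version may not contain the item. If so, the measure would still lack the nurses, and section 2.4.3 would have no clinician rating of this step to report.

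Third, physicians do contribute to the process: they supply the stratum, and section 2.4.1 plans to train them in stratification and randomisation. This justifies their rating those steps, but not the website lookup.

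Fourth, a reader might infer that a misleading percentage would carry a faulty procedure into the 760-child trial. The protocol ties no decision to this percentage. The main trial will also be placebo-controlled, so handing a prescription to one arm only belongs to this open-label pilot. That stronger consequence should not be claimed.

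None of this answers the narrow point: the ease rating is sought from, and reported for, the wrong group.

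**Conclusion.** The point holds in a limited form and is minor. The feedback measure of the allocation step omits its operators and is reported for a group that does not perform it. How difficult the website step is for the nurses is therefore not validly measured, although it falls within a named pilot objective. The size is one half of one of three components of procedure success. No treatment comparison, sample size or safety figure is touched.

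The conclusion rests on the protocol's description of the feedback form, which is not shown. If the actual form is already given to the nurses, only the wording of sections 2.4.1 and 2.4.3 needs correcting. The matter does not fall to a later analysis plan: the protocol itself fixes the raters and the reported group, and an analysis plan cannot recover ratings that were never collected.

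**What to change.** Three wording changes:

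- In section 2.4.1, add the appointed nurses as raters on the existing 1-to-5 form for the randomisation and allocation items.
- In section 2.4.3, report those items as the proportion of nurses giving each grade, with the number of nurses as the stated denominator.
- Limit the physicians' items to the steps they carry out: consent, eligibility, stratification and CRFs.

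The cost is one short form, already in use, completed by staff already in the study. No extra visits, staff or participant burden are needed.

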#### **2.4.2 Data management**

The integrity and completion of data will be maintained through mechanisms such as consistency checks during data entry, and cross-checks between items after data entry. All the actions and modifications to data stored in the database will be documented and retrievable for viewing. Missing data or errors will be detected before final submission to the electronic database and will be recorded in a summary along with the descriptions for each missing and/or error data. The summary will then be notified to the co-investigators in that hospital for further investigation by checking and confirming the original forms or other resources for correction or completion for those with missing and/or erroneous data. The modification to original forms will be done by research personnel at that hospital and will be documented on paper and electronic versions. It will be annotated with the date, name, and signature of the person who is responsible for making modifications.

The central data coordinator will check the validity and completeness of study data on a regular basis. All data in the central database will be protected with a regular complete back up system.

#### **2.4.3 Statistical methods**

For the recruitment rate, we report the outcome as the proportion of children in percentages (%). For the success of the study procedures and the ability to measure planned outcomes in main study, we will report the outcomes as the proportion of clinicians in percentages based on the grading

scale of their feedback reporting on prespecified outcome measure tools. For the compliance to study and study drug, we will report the outcomes as the proportion of children in percentages who attend the follow-up visits and complete the cycle of study drug.

To assess the verification of sample size calculation for main study, we will report this outcome as the proportion of children in each stratum (mild and severe AOM group) and those with pain at Day-3 after randomisation in the control group.

For the mechanistic sub-study, we will report continuous variables (i.e. the change in MEE at various time points (mean in days standard deviation), the duration of MEE) as a mean difference (MD) with 95% confidence intervals (CI) also the difference between two groups. We also will report the correlation between ear pain and other symptoms with the changes in MEE at various time points.

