| Outcome(s)              | 
(1) Outcome Name: Recruitment rates
 Metric/method of measurement: Informed consent form and case report forms (CRFs)
 The timepoint(s) of interest: Baseline visit (visit-0)
 
(2) Outcome Name: The success of the study procedures
 Metric/method of measurement: CRFs (i.e. eligibility and randomisation form, outcomes form)
 The timepoint(s) of interest: Baseline visit (visit-0)
 
(3) Outcome Name: Ability to measure planned outcomes in main study
 Metric/method of measurement: CRFs (i.e. eligibility and randomisation form, outcomes form) and symptom diary (e.g. Visual Analogue Scale/VAS and Acute Otitis Media – Severity of Symptoms Scale/AOM-SOS), and feedback form
 The timepoint(s) of interest: Baseline visit, visit-1 (day-3 to -5), visit-2 (day-7 to -9), day3, visit-3 (day-3 to -40), and visit-4 (day-90 to -100)
 
(4) Outcome Name: Compliance to study and study drug
 Metric/method of measurement: CRF (i.e. outcomes form), the symptom diary, and number of left-over drug
 The timepoint(s) of interest: Visit-1 (day-3 to -5), visit-2 (day-7 to -9), day3, visit-3 (day-3 to -40), and visit-4 (day-90 to -100)
 
(5) Outcome Name: The verification of sample size calculation for main study
 Metric/method of measurement: CRFs (i.e. eligibility and randomisation form)
 The timepoint(s) of interest: Baseline visit (visit-0)
 |

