### ***The success of the study procedures***

The success of the study procedures includes the following: (1) obtaining informed consent from the patients and their parents; (2) the recruitment based prespecified eligibility criteria, including the use of otoscope to diagnose AOM if feasible; and (3) the stratification and randomisation process, including stratifying eligible children based on the severity and obtaining the allocation result whether the children will be allocated to the prednisolone or control group.

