### ***Ability to measure planned outcomes in the main study***

We will assess the ability to measure planned outcomes in main study, which are: (1) the proportion of children with pain reduced by at least the minimum clinically important amount, at day-3 after randomisation. This will be assessed using a VAS recorded in the patient symptom diary; (2) the severity of pain and other AOM-relevant symptoms at various time points using VAS, AOM-SOS, and the symptom diary; (3) duration to AOM resolution; (4) adverse effects, defined using standard clinical trials criteria, recorded in the diary, and reported to the central office and ethics committee as required.; (5) complications of AOM (e.g. perforation of tympanic membrane(s), mastoiditis); and (6) AOM recurrence, defined as a new episode of AOM at one to three months after randomisation. We will report these narratively due to a limited sample size and insufficient formal power calculation for this pilot study to be able to detect actual effects of corticosteroids to improve clinical outcomes in AOM.

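### Success of the study procedures is defined as things done correctly but reported only as clinicians' ease ratings, and the ability to measure outcomes is also reported only as a rating

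*Protocol*

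**What the plan says.** Four places in the protocol bear on these two pilot outcomes.

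- **Definition (section 2.2.4.1).** Success of the study procedures has three parts: informed consent, recruitment on the prespecified eligibility criteria, and "the stratification and randomisation process, including stratifying eligible children based on the severity and obtaining the allocation result". Ability to measure planned outcomes covers the Day-3 pain result on the visual analogue scale (VAS), the AOM-SOS symptom scale, and other main-study outcomes.
- **Registration data set.** For procedural success the metric is "CRFs (i.e. eligibility and randomisation form, outcomes form"). For ability to measure it is the CRFs, the symptom diary and a feedback form.
- **Data collection (section 2.4.1).** "We will assess the success of the study procedures using feedback forms", with patients, parents and physicians rating "using grading scale ranged from one to five (1=very easy; 2= easy; 3=moderate/neutral; 4=difficult; 5=very difficult"). For ability to measure, "we will also use a feedback form to identify the understanding, the challenges, the complexity of the outcome assessment tools utilised for this study"; the text then describes what the CRFs and diary record.
- **Analysis (section 2.4.3).** For both outcomes, "we will report the outcomes as the proportion of clinicians in percentages based on the grading". The same sentence identifies this grading as the "scale of their feedback reporting on prespecified outcome measure tools". No other quantity is named for either.

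**The concern.** Assessing the main study's processes and procedures is the pilot's first objective (section 1.2). Section 1.1.3 explains why: most physicians in the main study will be new to trials, and AOM-SOS is not widely known among physicians in Indonesia. In that setting a user can find a form easy and still complete it wrongly, so an ease rating is a weak stand-in for correct conduct.

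The question the pilot was set up to answer is whether children were validly consented, eligible and correctly stratified and allocated, and whether their pain and symptom scores were usable. Under section 2.4.3 the results published under those two outcome names would not answer it. A reader planning the main study could take a favourable percentage as evidence of correct conduct when it shows only that clinicians found the tools easy.

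**Working it through.** The point rests on comparing texts. The plan gives no figure for either outcome, so there is none to reproduce.

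**1. Procedural success, component by component**

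| Component defined in 2.2.4.1 | Source in registration data set | What 2.4.1 and 2.4.3 use |
|---|---|---|
| Consent obtained | CRFs | Ease rating |
| Recruited on the eligibility criteria | CRFs | Ease rating |
| Stratified by severity, allocation obtained | CRFs | Ease rating |

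The reported quantity is (clinicians giving a particular grade) / (clinicians rating). No count of children appears in the numerator or denominator. Section 2.4.3 also words the rating as feedback on outcome measurement tools. Read literally, that does not cover consent, eligibility or stratification at all, although the form in 2.4.1 does ask about some of these procedures.

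**2. Ability to measure**

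The registration data set and 2.4.1 both bring in the CRFs and diary; in 2.4.1 the feedback form is an additional source. The gap opens in 2.4.3, where only the clinician rating is reported. Completion of the CRFs and diary is mentioned in 2.4.1 under compliance, but 2.4.3 reports compliance as visit attendance and completion of the drug course. Form completion therefore has no reported result under either heading.

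**3. Raters**

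Section 2.4.1 collects ratings from families and physicians; 2.4.3 reports clinicians only. This is a smaller mismatch in the same sentence.

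**4. Illustration of what each report can show**

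Inputs: 50 physicians with 30% taking part (worst case in the sample size section), so 0.30 × 50 = 15 raters; 60 children. The error counts are assumed. Intervals are exact (Clopper-Pearson). With x = n the lower limit is 0.025^(1/n), and with x = 0 the upper limit is 1 − 0.025^(1/n); otherwise both limits are beta quantiles.

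- All 15 clinicians rate the tools easy: 15/15 = 100%, lower limit 0.025^(1/15) = 0.78, so 78% to 100%.
- No child handled wrongly: 0/60 = 0%, upper limit 1 − 0.025^(1/60) = 0.06, so 0% to 6%.
- Twelve children handled wrongly: 12/60 = 20%, 11% to 32%.

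The first line can accompany either of the other two, because the number of errors is not part of its calculation.

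**The case against.** The strongest reply is that the protocol does not leave failures unseen.

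- Section 2.4.1 opens by naming CRFs, diary and feedback forms together as sources for the outcomes.
- Of the planned main-study outcomes, section 2.2.4.1 says "We will report these narratively due to a limited sample size". Widespread missing Day-3 pain scores would be hard to hide in such an account.
- Section 2.4.3 reports the proportion of children in each severity stratum and control-group pain at Day 3. Both need CRF data.
- The nurse checks returned diaries (2.2.3.3).
- Section 2.4.2 requires a summary of missing and erroneous data.
- Section 2.5.1 has an independent person review the quality of recruitment and data entry, with feedback intended for the main study.

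Much of this stands. The data will exist, and failures may come to light. A reader might infer that the pilot would declare full success while its procedures failed, but the documents do not support that: there is no pass mark, and nothing makes the rating decide what is restructured. Nor do they support saying that ratings are unrelated to errors. The two may be loosely associated; the protocol simply does not make one depend on the other.

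The reply does not reach the reported outcomes. The stratum proportions show how many children were placed in each group, not whether they were placed correctly. The narrative concerns clinical results and names no measure of completeness. The error summary exists so that records can be corrected, and neither it nor the independent feedback is tied to either outcome.

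A statistical analysis plan, not shown here, could add detail such as interval methods. The point does not depend on missing detail: the protocol names a measure that does not match its own definition.

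**Conclusion.** The concern holds in a bounded form. For procedural success the mismatch is complete: a definition in terms of events and a CRF metric on one side, clinicians' ease ratings alone on the other. For ability to measure it is partial: the sources include the CRFs and diary, but the only reported result is the rating.

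The effect is that two headline feasibility outcomes do not depend on what they are named for. Its size cannot be put as a bias or an error rate. The 15-rater and 60-child figures are illustrative and rest on the protocol's worst-case participation and on assumed error counts. The tympanometry comparison and its sample size are not affected. This is a moderate matter, well worth correcting because it concerns the pilot's first objective and the data needed are already planned.

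**What to change.** Reconcile the registration data set with sections 2.2.4.1, 2.4.1 and 2.4.3 so that each outcome has one definition, one source and one reported quantity.

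- **Success of the study procedures:** report proportions of children, from the CRFs and recruitment log book, with exact 95% confidence intervals: (a) consent form complete; (b) all eligibility criteria met on CRF review; (c) stratum and allocation consistent with the recorded severity features, which the protocol already lists under verification of the sample size.
- **Ability to measure planned outcomes:** report the proportion of children with a usable VAS and a usable AOM-SOS at Day 0, Day 3 and Day 7, the time points that Table 1 already schedules for both.
- **Ease ratings:** keep the 1 to 5 scores as separate acceptability information, which can help explain why a step failed. State whether families' ratings are reported alongside clinicians'.

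The cost is protocol wording and a few counts from forms already being collected. The reported results may look less favourable than the ratings would.
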